# Effectiveness and cost effectiveness of guided online treatment for patients with major depressive disorder on a waiting list for psychotherapy: study protocol of a randomized controlled trial

**DOI:** 10.1186/1745-6215-14-412

**Published:** 2013-12-01

**Keywords:** Depressive disorders, Internet-based treatment, Online guided self-help, Cost effectiveness, Outpatients, Specialized mental healthcare

## Abstract

**Background:**

Depressive disorders are highly prevalent and result in negative consequences for both patients and society. It is therefore important that these disorders are treated adequately. However, due to increased demand for mental healthcare and subsequent increased costs, it would be desirable to reduce costs associated with major depressive disorder while maintaining or improving the quality of care within the healthcare system. Introducing evidence-based online self-help interventions in mental healthcare might be the way to maintain clinical effects while minimizing costs by reducing the number of face-to-face sessions. This study aims to evaluate the clinical and economical effects of a guided online self-help intervention when offered to patients with major depressive disorder on a waiting list for psychotherapy in specialized mental health centers (MHCs).

**Methods:**

Patients at mental health centers identified with a *Diagnostic and Statistical Manual of Mental Disorders*, fourth edition (DSM-IV) diagnosis of major depression who are awaiting face-to-face treatment are studied in a randomized controlled trial. During this waiting list period, patients are randomized and either (1) receive an internet-based guided self-help treatment or (2) receive a self-help book. The 5-week internet-based guided self-help intervention and the self-help booklet are based on problem solving treatment. After the intervention, patients are allowed to start regular face-to-face treatment at MHCs. Costs and effects are measured at baseline, after the intervention at 6 to 8 weeks, 6 months and 12 months. The primary outcome measure is symptoms of depression. Secondary outcome measures are diagnosis of depression, number of face-to-face sessions, absence of work and healthcare uptake in general. Additional outcome measures are anxiety, insomnia, quality of life and mastery.

**Discussion:**

This study evaluates the effectiveness and cost effectiveness of internet-based guided self-help in patients at specialized mental health centers. The aim is to demonstrate whether the introduction of internet-based self-help interventions in regular mental healthcare for depressive disorders can maintain clinical effects and reduce costs. Strengths and limitations of this study are discussed.

**Trial registration:**

Netherlands Trial Register NTR2824

## Background

Depressive disorders are highly prevalent [1-3], and are associated with high costs in the professional, social, personal and financial realms [1,3,4]. Those suffering from depression are more often absent from work, and have higher levels of healthcare consumption compared to healthy individuals [2]. It is desirable from a clinical point of view to reduce the burden of depression, as it is from a societal point of view to reduce the economic costs related to increased healthcare uptake, and reduced work productivity. In addition, given the increased demand for mental healthcare and limitation of recourses, it is important for mental health centers to optimize the efficient and effective use of resources.

In The Netherlands, a person with symptoms of depression who is seeking help is most likely to be seen first by a general practitioner (GP) [5], who acts as a gatekeeper for referral to specialized mental health services. After registration at a mental health service, patients usually have an assessment and are then assigned to a specific treatment. The time between registration and the first treatment session is normally at least 6 weeks. Long waiting lists caused by low workforce numbers are common. This time might be used to deploy internet-based self-help treatments [6,7], as previous studies have indicated that internet-based self-help therapies are clinically effective in diverse populations [8-11]. Internet-based treatments require less therapist time in comparison with standard face to face treatments and can therefore offer potential solutions as they are immediately accessible, less costly and put less strain on therapeutic resources. They might serve first step in a stepped delivery of care. This means that only those who do not respond adequately step up to a treatment of higher intensity, in this case the regular treatment in mental health centers. This stepped-care approach is suggested in several guidelines such as the Australian and National Institute for Health and Care Excellence (NICE) guidelines for depression, which recommend that patients receive the least burdensome treatment. Psychological treatments such as computerized cognitive behavioral therapy (cCBT) and individual guided self-help programs are recommended as low intensity treatments. After receiving such treatments, patients possibly need fewer or no face-to-face sessions.

With the current cuts in healthcare budgets, it would be desirable to reduce costs associated with major depressive disorder while maintaining or improving the quality of care. Introducing evidence-based internet-based self-help interventions in mental healthcare might be the way to speed up clinical recovery while minimizing costs by reducing the number of face-to-face sessions. However, internet-based guided self-help interventions are currently not offered as a first step to those waiting for specialized mental healthcare.

In the current study, we offer an internet-based guided self-help program to patients on a waitlist for psychological treatment. The self-help program is based on problem-solving therapy and uses self-examination therapy as a general framework [12]. This method has been found to be effective in several studies in the US [13], and for this study we used a guided self-help program that has been examined in two earlier trials, and has proved its effectiveness in reducing depressive symptoms in community samples [14,15].

### Aims and hypotheses

This study aims to establish the effectiveness of an internet-based guided self-help intervention for patients with major depressive disorder before face-to-face treatment in specialized mental healthcare in comparison to a control group who are on a waitlist for face-to-face treatment. Furthermore, we expect that offering internet-based treatment as a first step of care reduces costs as we predict the internet group to take up fewer regular treatment sessions.

## Methods

### Study design

The study is a randomized controlled trial with an economic evaluation. We are currently enrolling 248 patients over 2 large mental health centers (MHCs) in 10 different locations. We will recruit patients directly after registration for regular face-to-face mental health services who need to wait for at least 6 weeks before their first treatment session. They will be randomized to either an internet-based guided self-help intervention or the regular waitlist before the first treatment session. People on the waitlist will receive a self-help book without additional guidance in order to motivate them to participate in the randomize, controlled trial (RCT). Both groups are allowed to receive regular face-to-face (FTF) therapy at the MHCs after the waitlist period. Participants in both groups complete assessment at baseline, at intervention or waiting list (WL) completion (6 to 8 weeks), at a 6-month follow-up, and at 12 months. The protocol of this study has been approved by the Medical Ethics Committee of the VU University Medical Center (registration number 2011/223).

### Inclusion and exclusion criteria

Eligible participants are adults, aged 18 or over, registering for regular treatment at one of the participating MHCs who meet the criteria for a *Diagnostic and Statistical Manual of Mental Disorders*, fourth edition (DSM-IV) diagnosis of major depression as measured with the Clinical International Diagnostic Interview (CIDI) by a trained research assistant, have access to the internet, and adequate proficiency in Dutch. Exclusion criteria are starting or changing type of dosage of antidepressant medication, the presence of a bipolar or psychotic disorder, and an increased risk of suicide. Comorbid disorders other than bipolar or psychotic disorders are allowed.

### Recruitment

Participants will be recruited while registering at the participating MHCs. In routine care patients are briefly scanned by the MHCs (according to MHCs protocol to screen out patients who are in crisis and need immediate treatment), and for the purpose of this study, patients with mood problems who are eligible for an intake assessment are asked by the MHC to share their contact details with the researchers. Those who are willing to do so, will then be called by a member of the research team who further explains the aim of this study and performs an additional check of the inclusion and exclusion criteria. If eligible, patients receive a study brochure and an informed consent form. Patients will only be included in the study if they meet all the criteria, and sign the informed consent form. In order to confirm the diagnoses Major Depressive Disorder trained interviewers conduct a clinical interview (CIDI).

### Sample size

The trial is powered to detect an effect size of d ≥0.40 [10,16] as statistically significant in a two-tailed test with α = 0.05 and power of (1 - β =) 0.80 with N = 99 per condition. To compensate for loss of follow-up of 20%, the trial requires starting with 99/0.8 = 124 participants per condition at baseline. The dropout rate of 20% is conservative, but from a power perspective a cautious approach. As this trial has two conditions, a total of N = 248 will be necessary for the complete trial.

### Mental health centers characteristics

Two MHCs will be participating in this research. They each offer services at a number of different locations. In this trial, a total of ten locations will participate. These centers are chosen for pragmatic purposes, as they have a high number of patient enrolment, and have participated in prior research of the VU University. In general, patients are referred by their general practitioner to the mental health centers where the patients is screened and placed on a waiting list. Within 6 weeks an initial meeting with a therapist takes place in which the patient’s needs and preferences regarding to treatment are determined. At these participating MHCs it normally takes between 7 to 16 weeks for patients to have a first treatment session, depending on therapist workload, treatment modality and other factors. Treatment in both centers can consist of psychological therapies such as CBT, sometimes in combination with medication. The researchers are not involved in the face-to-face treatment, and neither in the decision-making process. However, prior to the start of this study all therapists at the participating MHCs will be informed about the goals of this study and the internet-based intervention, they will attend a Q&A session with the first author and receive the self-help book containing the intervention. Prior to the start of a patients’ face-to-face treatment at the MHC the therapists will be informed by the aforementioned note in electronic patient record and through email that their patients are participating in this study. One of the objectives of the internet-based intervention is that the subsequent face-to-face treatment can be adjusted to fewer sessions. The number and type of therapeutic sessions patients will receive is based on the needs of the patient, the judgment of the therapist, and protocol available at the MHC. The type and number of sessions will therefore vary per participant, and are outside the control of the researchers.

### Internet intervention

The internet intervention that will be used is called 'Taking Control’ (original title: 'Alles Onder Controle’). This intervention uses the self-examination treatment model developed by Bowman and colleagues [12,13], which is based on problem-solving therapy and uses self-examination therapy (SET) as a general framework. We translated it into Dutch, elaborated on it, and added information and exercises. We built a website for this intervention and developed a system for email support. This intervention has been described in more detail in several other studies [12-14].

In brief, this intervention is short, structured and manualized. It consists of five weekly sessions. Each session contains a structured homework assignment to be completed by the participant. The first session requires participants to consider what is important in their lives. Next to this, participants will make a list of current problems and worries in their lives. This first session helps participants to divide their problems into the following three categories: not important (if the problem is not related to the list of important things), important and unsolvable (for example, permanent loss of health or a loved one), or important and solvable. In the second, third and fourth session participants will be offered various coping skills related to each of the categories of problems; the main focus is placed on adopting a structured six-step approach when encountering important, solvable problems. This structured approach is divided in the following steps: identifying the current problem; finding possible solutions; selecting one solution; create a plan to solve the problem with this solution; execute the plan and evaluate the plan. The last week of the intervention is reserved for both the reflection on long-term goals and the development of a structure to achieve these goals. Participants can only move on to the next session once the exercise in the current session has been submitted and when feedback on this session has been released by the research team.

The participants are supported by a coach, who gives feedback to the homework assignments of the participants in brief, weekly emails. The total amount of time spent on each patient is about 1.5 h (estimate based on our earlier trials). The writing of these emails takes about 15 or 20 minutes per week, and will be performed by a coach. The coaches will be trained by the psychologists who have developed the intervention and also wrote the protocol for giving feedback to ensure the consistency and integrity. An independent psychologist will verify whether the coaches have followed the protocol sufficiently by reading a random selection of the feedback emails.

The feedback has two purposes. Firstly, coaches will help participants to become familiar with the presented techniques. The second purpose consists of motivating the participant to continue with the intervention. Feedback will be received by participants within 3 working days after a session has been completed and submitted. When participants pose content related questions to their coaches via the website, email or phone, their coaches will provide additional guidance after receiving the question. After 5 weeks of guidance, patients can continue to use the internet-based treatment but will not receive any feedback on their assignments.

### Control condition

To increase participation rates in the control group, this group receives an unguided self-help book posted to their home address. This control group will not receive any feedback from coaches, nor will it have the opportunity to pose questions. Earlier research shows that self-help without any form of guidance only results in a small effect on participants with increased levels of depressive symptoms [16].

Participants in both conditions will be referred for regular FTF treatment after registration at the MHC. FTF treatment might consist of additional waiting time; the duration of the waiting time is highly variable with a minimum of 7 weeks and a maximum of 16 weeks depending on the location of MHC. Variation fluctuates both between locations and over time within the centers, due to availability of therapists. In case the waiting time for any MHC falls below 8 weeks, new participants from this MHC will be temporarily excluded from participating in the research until the waiting time for new patients at this MHC exceeds 8 weeks again. This has been decided in order to not measure the effects of active treatment by the MHCs at the first post-intervention test at 8 weeks.

The researchers of this study do not influence the waiting time at the MHCs, nor will participation in this study influence the waiting time for the participants.

### Randomization and blinding

The random allocation sequence will be generated by an independent researcher in the program 'Random Allocation Software’, stratified by location using blocks of six, eight and ten. After each inclusion another independent researcher will allocate the patient to either the intervention or the control condition. Due to the nature of the intervention the treatment group allocation cannot be concealed from the participants, nor from the research team and assessor of outcomes. Participants are assigned to one of two conditions within 2 working days from their baseline assessment Figure 1.

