### Statistical analysis

The analyses will be conducted in agreement with the intention to treat (ITT) principle, as per the CONSORT statement [34]. Therefore missing endpoints will be imputed using state of the art imputation methods, as a reliable method for handling missing values [35]. Imputation allows for analyzing all participants in the condition to which they have been randomized, which contributes to guarantee the integrity of the randomization and restores loss of power due to dropout.

To answer the research questions we will first look at post-test differences between the two groups. We will use analysis of variance (ANOVA), with the baseline values and waiting time as covariates. Subgroup analyses will be performed for different characteristics. The difference in scores between the intervention group and the control group will also be expressed in effect sizes. We use Cohen’s *d* which is calculated by dividing the difference in mean scores of the two groups by their pooled standard deviation (Xexp-Xctrl/SDpooled). Effect sizes under 0.2 are considered to be small, those of 0.5 are moderate and effect sizes of 0.8 are considered to be large [36]. Furthermore, we will compare the rate of DSM-IV diagnosis of depression in both groups with logistic regression analysis. The clinical effects will also be calculated using reliable change [37]. The long-term outcomes will be analyzed with longitudinal analyses.

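### Randomisation is stratified by location, but location is not among the stated covariates of the primary post-test model; if location is prognostic, the test is slightly conservative

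*Protocol article*

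**What the plan says.** All references are to the Methods of the protocol article.

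- *Randomization and blinding*: allocation is "stratified by location using blocks of six, eight and ten".
- *Mental health centers characteristics*: "a total of ten locations will participate".
- *Statistical analysis*, on the post-test difference: "We will use analysis of variance (ANOVA), with the baseline values and waiting time as covariates". Location is not mentioned there or elsewhere in the analysis text.
- *Control condition*, on waiting time: "Variation fluctuates both between locations and over time within the centers, due to availability of therapists".
- *Sample size*: "The trial is powered to detect an effect size of d ≥0.40", in a "two-tailed test with α = 0.05 and power of (1 - β =) 0.80 with N = 99 per condition". The number is then inflated for 20% loss to follow-up. The calculation takes no credit for covariates or stratification.

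**The concern.** The design balances the arms within each location, but the stated model does not use that balance. Stratified blocks take between-location differences out of the treatment contrast. A model without location leaves the same differences in the residual variance. The reported standard error then describes a less precise comparison than the one carried out: the interval is too wide, the p-value too large, and some attainable power is unused.

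This is more than detail left to a later document, because the article does give a covariate list and the one stratification factor is missing from it. There is also some reason to expect locations to differ. The article says that waiting and therapist availability vary between them, and location was thought important enough to stratify on.

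**Working it through.** **1. The plan's own figure.** With d = 0.40, two-sided α = 0.05 and power 0.80:

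n = 2 × (1.96 + 0.8416)² / 0.40² = 98.1, rounded up to 99 per arm. Then 99 / 0.8 = 123.75, rounded up to 124, and 2 × 124 = 248. All three figures reproduce. Normal-approximation power at 99 per arm is 80.35%; the t-test version gives 79.97%.

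**2. Inputs for the check.** Ten locations, blocks of 6, 8 and 10, 99 per arm and d = 0.40 come from the article. The one assumption is ρ, the share of residual CES-D variance (after baseline and waiting time) that lies between locations. The article gives no value, so a range of 0 to 0.10 is shown.

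**3. Formulas.** On the residual SD scale, SE = √(2/99) = 0.1421. Under stratified blocks the true standard error is about SE × √(1 − ρ), while the model without location reports about SE.

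- Overstatement of the standard error: 1/√(1 − ρ)
- Power without location: Φ[(0.40 − 1.96 × SE) / (SE × √(1 − ρ))]
- Power with location: Φ[0.40 / (SE × √(1 − ρ)) − 1.96]
- True type I error without location: 2 × [1 − Φ(1.96 / √(1 − ρ))]

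Example, ρ = 0.05: √0.95 = 0.9747 and 0.40/0.1421 = 2.814. Without location, Φ(0.854/0.9747) = Φ(0.876) = 80.96%. With location, Φ(2.887 − 1.96) = Φ(0.927) = 82.31%.

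| ρ (assumed) | SE overstated by | Type I error without location | Power without location | Power with location | Gain (points) |
|---|---|---|---|---|---|
| 0 | 0% | 5.0% | 80.35% | 80.35% | 0 |
| 0.01 | 0.5% | 4.9% | 80.47% | 80.74% | 0.27 |
| 0.02 | 1.0% | 4.8% | 80.59% | 81.13% | 0.54 |
| 0.05 | 2.6% | 4.4% | 80.96% | 82.31% | 1.35 |
| 0.10 | 5.4% | 3.9% | 81.61% | 84.29% | 2.68 |

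The formulas ignore the degrees of freedom spent on location, so a simulation was used as a check.

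**4. Simulation.** 198 evaluable patients, ten locations, blocks of 6, 8 and 10, and 4,000 runs per setting. Both models include baseline and waiting time.

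| Setting | Mean reported SE without / with location | Power without / with location |
|---|---|---|
| ρ = 0 | 0.1426 / 0.1431 | 78.8% / 78.7% |
| ρ = 0.05 | 0.1426 / 0.1395 | 79.8% / 81.1% |
| ρ = 0.10 | 0.1422 / 0.1356 | 80.6% / 83.2% |
| ρ = 0.05, waiting time sharing about half the location signal | 0.1417 / 0.1395 | 79.5% / 80.2% |

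At ρ = 0 the nine extra parameters cost about 0.2 points (78.83% against 78.67%). Simulated type I error without location was 4.5% at ρ = 0.05 and 4.3% at ρ = 0.10. This agrees in direction with the formula, given a Monte Carlo standard error of √(0.05 × 0.95 / 4000) = 0.34 points.

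**The case against.** **Nothing planned is undermined.** The sample size takes no credit for covariates or stratification, the estimate is unbiased, and the error is conservative. All of this stands and limits the point to efficiency and coherence.

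**The harm is conditional.** A reader might infer that the interval and p-value will certainly be wrong and that power is being thrown away. The article does not support that. The loss exists only if location explains CES-D variance after baseline and waiting time, and no figure for this is given.

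**Waiting time may already do part of the work.** The article says waiting differs between locations, so the existing covariate is a partial proxy. With half the signal shared at ρ = 0.05, the simulated gain falls to about 0.7 points. It is only partial, because waiting also changes over time within centers.

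**The gain is easily overstated.** Comparing power with location against the 80.35% of the plan's own calculation gives 81.13 − 80.35 = 0.8, 82.31 − 80.35 = 2.0 and 84.29 − 80.35 = 3.9 points at 2, 5 and 10%. That comparison is not a fair one: stratification also lifts the model without location above its planned power, so the true gains are about 0.5, 1.4 and 2.7 points.

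**The point does not extend to the other analyses.** A reader might carry it to the logistic, longitudinal and cost analyses. The article states no covariates for those, and an article commonly leaves that detail to the full plan. In logistic regression the mechanism also differs, since adjustment changes the odds ratio being estimated. Nor does the omission of location give a reason to remove waiting time as a biased covariate; the article says participation does not influence waiting time.

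**An analysis plan not shown may already include location.** It may, but the article states a covariate list, and that list does not match the randomisation.

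**Conclusion.** The point holds as a minor correction to the primary post-test CES-D model. The stated covariates omit the factor by which randomisation is stratified. For an assumed 2 to 10% of residual variance between locations, the standard error is overstated by 1.0 to 5.4%, the true type I error is about 4.8 to 3.9%, and about 0.5 to 2.7 points of power are unused. Sharing of the location effect with waiting time reduces these figures, and at 0% there is a loss of about 0.2 points from adding the term. The omission itself is certain from the text. The size of its effect is not, because it depends wholly on an unreported between-location variance.

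**What to change.** In *Statistical analysis*, add location (10 levels, as a fixed effect or a random intercept) to the stated covariates of the primary post-test CES-D model, keeping baseline values and waiting time. If location is left out on purpose, say why.

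The cost is one model term and up to 9 degrees of freedom out of about 196 (198 evaluable patients less 2). Location is already recorded for the randomisation. *Trial status* gives recruitment as ongoing, so the term can still be specified in advance. The sample size does not change.
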